# Laboratory Assays

The following laboratory tests will be obtained at baseline, 1 year and 5 years. The majority of these tests form part of routine clinical care and would normally be performed annually by the General Practitioner. Tests marked with an asterix are not routine and will be performed by the researcher in a research laboratory. Participants will be asked not to eat meat for 12 hours prior to the blood tests (to avoid a potential effect on the creatinine assay).

- Urea and electrolytes
- Estimated GFR
- Calcium and phosphate
- Serum albumin
- Lipid profile
- Random blood glucose
- Bicarbonate
- Uric acid
- Full blood count
- Urine albumin:creatinine ratio (on three early morning specimens)
- Urine protein:creatinine ratio (on three early morning specimens)
- Urine sodium (on three early morning specimens)
- Urine phosphate (on three early morning specimens)
- 24h urine collection for measurement of urinary creatinine, protein, albumin, sodium and phosphate will be performed in a subgroup of 160 patients.
- High sensitivity C-reactive protein (CRP)
- ADMA (asymmetrical dimethyl arginine)
- Serum fibroblast growth factor 23 (FGF 23)*
- Serum 25 hydroxy-vitamin D
- Serum 1,25 dihydroxy-vitamin D
- Serum Parathyroid hormone
- Serum Cystatin C
- Serum free light chains
- Serum will be stored for future biochemical assays but these will not include genetic testing. This to allow testing of substances that may be identified as significant risk factors for renal or cardiovascular outcomes during the follow-up period. Serum will not be stored beyond the duration of the study.

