## Sample Size Determination

The sample size was estimated based on two similar studies, one for predicting renal outcome in IgA nephropathy [4] and the other in patients with type 2 diabetes and nephropathy [3]. Based on these studies the smaller event rate was 12% and the smallest significant Hazard Ratio was 1.2. Therefore the total sample size for this study, using the Cox Proportional Hazards models with Power 80% and at significant level 5%, is 1968. Assuming death rate during the 5 years of 3% and drop out rate of 10% the final total sample is 2255. We plan to complete recruitment in 1 year and therefore aim to recruit approximately 190 participants per month. CKD stage 3 is estimated to affect at least 5% of the UK population. There should therefore be approximately 35,000 patients available for recruitment in Derbyshire.

A separate sample size estimate was performed for the sub-study comparing spot early morning urine biochemistry with that from 24hour urine collections. Based on previously published data, we calculated that a sample of 160 would allow us to show a correlation co-efficient of 0.9 with precision of the estimate of 0.03 at 80% power with a significance of 5% [7].

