## Statistical Methods

Basic demographic data will be retained on the anticipated small number of excluded patients as these form part of the at risk population. Descriptive statistics will be used to provide a summary of each of the variables collected at each time point. Multivariable linear regression analysis will be used to assess the effect of baseline variables as well as changes in these variables over the first 12 months on changes in blood pressure, proteinuria and glomerular filtration rate. Cox proportional hazards models will be used to identify independent baseline risk factors for CKD progression and cardiovascular events at 5 and 10 years. A similar method will be used to assess the possibility that changes in baseline variables from baseline to 12 or 24 months may be better predictors of CKD progression and cardiovascular events than baseline variables alone. Coefficients derived from Cox proportional hazards analysis for the independent determinants of CKD progression or cardiovascular events will then be used to produce a risk scoring system.

In a subgroup of 160 patients, assessment of proteinuria by urine protein to creatinine ratio versus albumin to creatinine ratio or 24h urinary protein will be assessed. Intraclass Correlation Coefficients will be used for comparing the three methods and Bland-Altman plots will be performed. 24 hour urinary protein will be the standard against which the other methods are compared. Similar analysis will be performed to compare urinary sodium and phosphate assays in spot and 24 hour urine specimens.

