Estimated GFR values obtained with a new creatinine-cystatin-C equation [12] will be compared to eGFR derived from creatinine alone using a paired t-test to compare the mean values and by Bland-Altman plots. The intraclass correlation coefficients (95% Confidence Interval) will be used to check the agreement of eGFR estimates by different equations. The analysis will be repeated in clinically important subgroups including participants under 75 years versus 75 years or older, males versus females and those with diabetes versus those without. The change in eGFR over 5 years determined by each of the GFR estimating equations will be similarly compared. We will compare the performance of prognostic models using eGFR derived from creatinine versus combined creatinine-cystatin-C equation with respect to discrimination (C-statistic derived from ROC curves) and calibration (Hosmer Lemeshow test, net reclassification index (NRI)). We will repeat these analyses using change in GFR (estimated from creatinine or combined equations) and albuminuria over the first year of follow-up as independent variables as well as baseline values to test whether change over the first year adds to the prognostic model.

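### First-year change is compared only with baseline values, so a gain cannot be attributed to change rather than to having a second reading

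*Protocol*

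**What the plan says.** Section 8.2 (Statistical Methods) takes up first-year change twice.

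- The Cox paragraph will examine whether changes in baseline variables "may be better predictors of CKD progression and cardiovascular events than baseline variables alone".
- The paragraph on GFR equations states: "We will repeat these analyses using change in GFR (estimated from creatinine or combined equations) and albuminuria over the first year of follow-up", and enters these changes "as independent variables as well as baseline values to test whether change over the first year adds to the prognostic model". The models there are compared on "discrimination (C-statistic derived from ROC curves) and calibration (Hosmer Lemeshow test, net reclassification index (NRI").

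Section 5 (Laboratory Assays) fixes the data available: "The following laboratory tests will be obtained at baseline, 1 year and 5 years". The first year therefore holds two study visits. Albuminuria is replicated within a visit, "Urine albumin:creatinine ratio (on three early morning specimens"); no such replication is stated for serum creatinine or cystatin C.

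Nowhere does the protocol compare change with the mean of the two readings or with the year-1 level, and it does not mention measurement error or regression dilution.

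**The concern.** A single reading is an imprecise measure of a patient's usual GFR or albuminuria. Adding change to a model that already holds the baseline reading brings in a second reading of the same quantity. Even if every patient's true level moved by the same amount, the second reading would sharpen the estimate of that level, and change would appear to predict outcome.

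Two messages for primary care are then confounded: that a patient whose values worsen over a year is at higher risk, and that one reading is imprecise and should be repeated. The distinction matters here because assessing the value of monitoring urine albumin to creatinine ratio is one of the objectives in section 2. The problem applies to both primary endpoints. Starting follow-up at 12 months, or choosing a different performance measure, would not remove it.

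**Working it through.** **Inputs from the protocol.** 1822 subjects (Study Summary). From section 8.1: "Based on these studies the smaller event rate was 12% and the smallest significant Hazard Ratio was 1.2"; and the total, "using the Cox Proportional Hazards models with Power 80% and at significant level 5%, is 1968". The protocol gives no figure for the test of first-year change.

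**The plan's own figure.** For a continuous covariate per 1 SD, two-sided 5% and 80% power:

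- Events = (1.95996 + 0.84162)² / (ln 1.2)² = 7.8489 / 0.03324 = 236.1.
- N = 236.1 / 0.12 = 1967.7, i.e. 1968, as stated.
- 1968 / (0.97 × 0.90) = 2254.3, i.e. 2255, as stated.

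The planning hazard ratio of 1.2 therefore reads as per SD of a continuous marker, and is used that way below. Expected events in 1822 patients: 1822 × 0.12 = 218.6.

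**Algebra.** Let B be the baseline reading, Y the year-1 reading and C = Y − B. Then b·B + c·C = (b − c)·B + c·Y, so the two parametrisations are one model. If the true level is constant and both readings carry equal independent error, the best predictor is proportional to B + Y = 2B + C. The coefficient of C is half that of B, not zero. Simulation agrees: 0.612 for B and 0.300 for C at HR 2.0 and reliability 0.8.

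**Closed-form size.** Assumptions, none given in the protocol: true GFR mean 47 and SD 8 ml/min, within-person error 8%.

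- Error variance = (0.08 × 47)² = 14.14.
- Reliability of one reading = 64 / (64 + 14.14) = 0.819.
- Reliability of the two-visit mean = 64 / (64 + 7.07) = 0.901.
- Non-centrality of the 1-df test of C given B ≈ 218.6 × (ln HR)² × (0.9005 − 0.8191).

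| HR per SD of true level | Non-centrality | Chance that change is significant (closed form) | Same, simulated |
|---|---|---|---|
| 1.2 | 0.59 | 12% | 11–14% |
| 1.5 | 2.93 | 40% | 37–44% |
| 2.0 | 8.56 | 83% | 82–83% |

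**Sensitivity to reliability** (simulated, 1822 patients, 12% events, true level constant):

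| HR | 0.95 | 0.9 | 0.8 | 0.7 | 0.6 |
|---|---|---|---|---|---|
| 1.2 | 6% | 8% | 15% | 15% | 18% |
| 1.5 | 13% | 26% | 47% | 52% | 64% |
| 2.0 | 39% | 64% | 87% | 95% | 96% |

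As a check, HR 1.0 at reliability 0.8 gives 4%. At HR 2.0 and reliability 0.8, event rates of 3%, 5% and 25% give 33%, 48% and 100%.

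**Planned measures.** At HR 2.0, reliability 0.8 and 12% events, the C-statistic rises by 0.010 on average and a category-free NRI is significant in 65% of runs.

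**Change given the two-visit mean.** With equal error at both visits, change is significant in about 3–7% of runs at 12% events, close to the nominal 5%. With error of 10% at baseline and 6% at year 1 (variances 22.09 and 7.95) this no longer holds. The optimally weighted pair has reliability 0.916 and the simple mean 0.895, so at HR 2.0 the non-centrality is 218.6 × 0.4805 × 0.0213 = 2.24, and change is significant about 32% of the time although nobody changed differentially.

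**Limits.** One marker, no other covariates, and follow-up not restarted at year 1. Restarting would leave fewer events and lower these rates.

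**The case against.** The strongest reply is that the protocol asks a prognostic question. Baseline plus change, baseline plus year-1 and mean plus change give identical fitted risks and C-statistics, so a gain over baseline is a real gain in prediction. This stands. A reader might infer that the planned test produces false positives or that the risk score would be wrong. Neither follows, because the score is the same under any of these parametrisations. What remains is the attribution of the gain to change.

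A reader might also infer that the most recent value alone would do as well. In this scenario it would not: year-1 and baseline readings are interchangeable. One simulation at HR 2.0 gave C of 0.672 for baseline, 0.671 for year-1, 0.679 for the mean and 0.680 for both readings.

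A third tempting step is to let change count only if it is significant given the mean. That fails in both directions. The 5% level needs equal error at both visits, and power for a real effect is low: roughly 20–60% at HR 2.0 with a true-change SD of 3–5 ml/min, against about 99% for the planned comparison.

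The objections about size also hold in part. At the only hazard ratio in the document the effect is modest. Identical true change in everyone is a limiting case, and section 1.1 itself describes heterogeneous risk of decline. The rejection rates come from significance tests of the coefficient, while section 8.2 names other measures for its model comparison. Three urine specimens per visit lessen the effect for albuminuria.

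Finally, extra comparators can be left to an analysis plan. Here, though, the protocol text itself fixes both the comparator and the question it is meant to answer.

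**Conclusion.** The concern holds as a limit on interpretation. Judged against baseline values alone, a gain from first-year change cannot be separated from the gain of measuring twice. With 8% error and 12% events, change would be significant without any differential true change in about 12% of studies at HR 1.2, about 40% at 1.5 and about 80% at 2.0. The effect is therefore small for weak markers and large for strong ones. The 1822 patients, the 12% and the HR of 1.2 are the protocol's; the GFR distribution, the error size and the larger hazard ratios are assumed. The documents do not support a claim that the planned models predict wrongly. Adding the missing comparator is an inexpensive improvement.

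**What to change.** In both paragraphs of section 8.2, specify four models fitted to the same patients, with follow-up from the 12-month visit: baseline value only; year-1 value only; mean of the two values; and that mean plus change. Then:

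- Report the step from baseline to the two-visit mean as the gain from a repeat measurement.
- Report the coefficient of change given the mean, with its confidence interval, and note that its interpretation assumes similar error at both visits.
- State that a gain over baseline alone will not be described as evidence that change itself is prognostic.
- Do not make significance given the mean a pass/fail rule.

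The cost is some wording and a few extra models on data already collected. The downside is a less clear-cut statement about change, because the coefficient given the mean will be estimated with limited precision.

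### Protocol 8.2 tests whether first-year change adds to the baseline model by repeating a C-statistic, Hosmer-Lemeshow and NRI comparison on nested models, and none of these is a sound test of the added terms

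*Protocol*

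**What the plan says.** The last paragraph of Statistical Methods (Protocol 8.2) first compares prognostic models using creatinine-based eGFR with models using the combined creatinine–cystatin-C eGFR. The yardsticks are "discrimination (C-statistic derived from ROC curves) and calibration (Hosmer Lemeshow test, net reclassification index (NRI". Those are alternative models, and neither contains the other.

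The same analyses are then to be repeated with change in GFR and in albuminuria "over the first year of follow-up as independent variables as well as baseline values", the stated purpose being "to test whether change over the first year adds to the prognostic model". The comparison is now baseline against baseline plus change, so one model contains the other. Two change variables are named. The section gives no test formula for a difference in C, no type of NRI or cut-points, and no measure that decides.

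An earlier paragraph of the same section plans Cox models to assess whether changes to 12 or 24 months "may be better predictors of CKD progression and cardiovascular events than baseline variables alone". The later paragraph does not refer back to it.

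**The concern.** The hypothesis is that, once baseline values are in the model, the change terms contribute nothing, so their coefficients are zero. The usual reference distributions for a difference in C and for the NRI treat the two risk scores as fixed and given. When the models are nested and the hypothesis is true, the two fitted scores converge on each other. The C difference is then not approximately normal around zero, and its standard test becomes very conservative. The category-free NRI is pushed upward, because the extra coefficients were fitted to the same outcomes that score them. Hosmer-Lemeshow checks the fit of one model and says nothing direct about added terms.

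At stake is whether a year of monitoring improves prediction, which bears on the study objective about the value of monitoring UACR. A real contribution could be declared absent from the C-statistic, or a null one declared useful from the category-free NRI. No primary endpoint and no sample size depends on this comparison.

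**Working it through.** **Inputs from the protocol.** N = 1822 (Study Summary). From Sample Size Determination (8.1): "the smaller event rate was 12% and the smallest significant Hazard Ratio was 1.2", and the sample size "using the Cox Proportional Hazards models with Power 80% and at significant level 5%, is 1968". Two added variables (8.2).

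**The protocol's own figure.** For a Cox model with one continuous covariate of SD 1:

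- events = (z₀.₉₇₅ + z₀.₈₀)² / (ln 1.2)² = 7.849 / 0.033241 = 236.12
- N = 236.12 / 0.12 = 1967.7, so 1968, as stated
- 1968 / (0.97 × 0.90) = 2254.3, so 2255, as stated

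The figure reproduces with the hazard ratio of 1.2 read as per SD, so an effect of 1.2 per SD is a fair benchmark for an added term.

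**Assumptions not in the protocol.** DeLong as the C-statistic test; the usual z-test for the NRI; two-sided 5%; a fixed-horizon binary outcome with logistic models and no censoring, standing in for Cox; and all measures scored on the fitting data. Categorical NRI cuts were 5/10/20% or 10/20%. Baseline models had 1, 4 or 8 covariates with linear-predictor SD 0.8 or 1.3. Added terms were correlated −0.3 with baseline. There were 2000 data sets per setting, with about 1822 × 0.12 = 219 events each.

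**Tests.**

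- Likelihood ratio: 2(ℓ₁ − ℓ₀), with ℓ₁ and ℓ₀ the maximised log-likelihoods with and without the change terms, against χ² on 2 df (5% point −2 ln 0.05 = 5.99)
- DeLong: z = (C₁ − C₀)/SE
- Category-free NRI: [P(up | event) − P(down | event)] + [P(down | no event) − P(up | no event)], divided by its SE

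**Null true: rejection at nominal 5%, 12% events**

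| Test | One added term | Two added terms |
|---|---|---|
| DeLong | 0.1–0.3% | 0.4–0.7% |
| Category-free NRI | 5.1–8.4% | 12.9–18.6% |
| Categorical NRI | 2.8–5.3% | 4.5–7.8% |
| Likelihood ratio | 4.6–6.6% | 4.6–6.3% |

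For the category-free NRI with two terms this is 12.9/5 = 2.6 to 18.6/5 = 3.7 times nominal. At event rates of 5% and 20% with two added terms, DeLong rejects about 0.5% and 0.2%, and the category-free NRI 12% and 14%.

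**Two added terms with a true effect of 1.2 per SD** (odds ratio in place of hazard ratio; 4 baseline covariates, linear-predictor SD 1.0)

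| Test | One term real | Both real |
|---|---|---|
| DeLong | 9% | 26% |
| Category-free NRI | 57% | 81% |
| Categorical NRI | 9–17% | 18–33% |
| Likelihood ratio | 52% | 83% |

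Further simulations at the same N, event rate and number of added terms gave, under the null, DeLong 0.2–0.3% and category-free NRI 12–18%. Power for DeLong against the likelihood-ratio test was 8–12% against 50–54% (one term real) and 22–28% against 82–84% (both real).

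**Do the measures agree?** DeLong and the category-free NRI give opposite verdicts in 13–18% of null data sets with two added terms, in 48% when one term is real, and in 56% when both are.

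**The case against.** The strongest reply is that the protocol lists performance measures, not test formulas. The type of NRI, its cut-points and the inference on a change in C are details a statistical analysis plan may supply, and their absence is no fault. That stands, and it limits the claim: the rejection rates are conditional on the assumed formulas. It does not remove the point, because the section states both the question to be tested and the tools for answering it, and those tools were carried over from a non-nested comparison.

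A reader might infer that the NRI would reject about three times too often whatever is done. The documents do not support that. The factor needs the category-free NRI, both change terms, and scoring on the fitting data; the protocol does not say which NRI is meant.

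A reader might also infer that no valid assessment of change variables is planned, or that the 12- or 24-month Cox paragraph has the same fault. Neither follows. That paragraph specifies Cox regression and mentions neither C nor NRI, and models containing the change terms can yield a test of them directly. What is missing is the link between that assessment and the question in the later paragraph.

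It is also fair to say that nonzero coefficients and a material gain in prediction are different questions. That is a reason to keep C and NRI as measures of size, not to use them as the test.

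**Conclusion.** The concern holds in a limited form. The C-statistic result is the firmest part. Judged by DeLong, the nested comparison rejects well under 1% under the null with two added terms, at every baseline strength and event rate tried. Where one term has an effect of 1.2 per SD it has about 8–12% power, against about 50–54% for the likelihood-ratio test. NRI inflation to about 12–19% is confined to the category-free form with both change terms on the fitting data. With no deciding measure named, the conclusion can depend on which one is read.

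The figures rest on uncensored logistic models in place of Cox, on assumed baseline strength and correlation, and on all 1822 patients contributing. Fewer patients with year-1 values would lower the power of every test. The change is worth making, but it affects a secondary prognostic question and not the main endpoints.

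**What to change.** In the last paragraph of Statistical Methods (8.2), replace the closing clause with wording such as:

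> *Whether change over the first year adds to the baseline prognostic model will be tested by a likelihood-ratio test (2 df: change in GFR, change in albuminuria) between nested Cox models with and without the change terms, fitted in the same patients, as part of the Cox assessment of change variables described above. The change in C-statistic and the NRI will be reported as descriptive, optimism-corrected measures of the size of the gain. No p-value, and no rule based on an interval excluding zero, will be applied to them.*

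The last two sentences matter. A bootstrap that merely refits both models in each resample does not cure the problem. With two null terms (N=1822, 12% events, 400 data sets per setting, 200 resamples), 95% percentile intervals lay wholly above zero in 12.5–14% of data sets for the category-free NRI and in about 6–10% for the C difference, against 2.5% expected in that tail.

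The cost is one or two sentences. No new data are needed, and the test comes with the Cox models already planned. The small downside is that a significant likelihood-ratio test can accompany a very small gain in C, so the descriptive measures must be reported beside it.

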## Subject Population(s) for Analysis

All patients will be included in the analyses described above except for the analyses that include results derived from 24 hour urine collections (subgroup of 160 patients only). Data from patients who withdraw (and give consent) or who die will be included until the date of withdrawal or death. Analyses of data from 24 hour urine collections will be applied only to the relevant subgroup.

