## To assess associations between CKD and a wide range of previously described risk factors.

# Study Design

## General Design

This is a long-term longitudinal observational cohort study.

Patients will be followed for 10 years. Clinical assessments will take place as described at baseline, 1 year and 5 years. After this patients will no longer be assessed clinically but outcome data with respect to the primary end points as well as survival will be collected. The Medical Research Information Service (MRIS) will (an arm of the NHS Information Centre), will be used to accurately track survival data of participants.

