## Withdrawal of Subjects

Patients will be withdrawn only if they withdraw their consent.

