### Data Collection and Follow-up for Withdrawn Subjects

Patients who withdraw will be asked to allow data collected prior to the date of withdrawal to be retained for analysis. They will also be asked to allow outcome data, including clinical events and the results of any kidney function tests arranged by the GP, to be collected for future analysis. If a participant declines this their data will be deleted.

Patients who fail to attend for follow-up will be contacted by telephone to determine whether or not they are willing to continue. Patients without access to a telephone will be contacted by letter. If no response is received to two letters sent one month apart, the patient will be assumed to have been lost to follow-up.

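### Section 8.3 stops withdrawers' data at the withdrawal date, although section 4.3.2 asks them to allow outcomes to be collected afterwards for analysis

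*Protocol*

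**What the plan says.** Section 8.3 (Subject Population(s) for Analysis) puts all patients into the analyses, apart from the 24-hour urine work, and then limits what withdrawers contribute: "Data from patients who withdraw (and give consent) or who die will be included until the date of withdrawal or death".

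Section 4.3.2 makes two separate requests of a withdrawing patient. The first is to keep the data already collected. The second looks forward: "They will also be asked to allow outcome data, including clinical events and the results of any kidney function tests arranged by the GP". Its stated purpose is later analysis. For refusal it adds: "If a participant declines this their data will be deleted".

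On patients who simply stop attending, section 4.3.2 provides for contact by telephone, or by letter for those without a telephone, and then says: "If no response is received to two letters sent one month apart, the patient will be assumed to have been lost to follow-up". Section 4.3 states: "Patients will be withdrawn only if they withdraw their consent".

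Section 3.1 ends clinical assessment after year 5 but continues ascertainment: "outcome data with respect to the primary end points as well as survival will be collected". The national records service (MRIS) "will be used to accurately track survival data of participants".

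**The concern.** The protocol asks withdrawing patients for permission to collect their later clinical events and kidney function results, and then fixes an analysis rule that has no place for them. Those results bear directly on both primary endpoints: doubling of creatinine or renal replacement therapy, and cardiovascular events.

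Two things are at stake. The first is precision, because events that could be counted are not. The second is validity. Section 8.2 turns Cox coefficients into a risk score and assesses the calibration of prognostic models, and calibration depends on complete event capture. If patients who withdraw have a different risk from those who stay, and the model's covariates do not account for it, stopping their follow-up at withdrawal distorts absolute risk.

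**Working it through.** **The passages side by side**

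| Patient | Section 4.3.2 | Section 8.3 |
|---|---|---|
| Withdraws, agrees to both requests | Earlier data kept; later outcomes collected for analysis | Data used only up to withdrawal |
| Withdraws, declines | Data deleted | Not included |
| Stops attending, does not reply | Assumed lost to follow-up | No cut-off stated; falls under all patients |

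The conflict is in the first row. The third row is a gap, not a conflict.

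**The plan's own figures** (section 8.1: event rate 12%, hazard ratio 1.2, power 80%, significance level 5%, deaths 3%, drop-out 10%). Read as a hazard ratio per standard deviation of a covariate with a two-sided test, neither of which is stated:

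- events = (1.960 + 0.842)² / (ln 1.2)² = 236.1
- N = 236.1 / 0.12 = 1967.7, so 1968
- 1968 / (0.97 × 0.90) = 2254.3, so 2255

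The figures reproduce. The inflation treats drop-outs as contributing no events.

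**Upper bound on events lost.** Inputs: 1822 subjects (Study Summary); 10% and 12% (section 8.1). Assumptions: 12% is a 5-year risk (the protocol gives no time horizon); the hazard is constant to year 10; all drop-outs are withdrawers; they leave evenly over 5 years; all allow outcome collection; their risk is average; deaths are ignored.

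- Drop-outs: 0.10 × 1822 = 182
- Hazard: −ln(0.88) / 5 = 0.0256 per year
- S(5) = 0.88; S(10) = 0.88² = 0.774
- Mean of S over 0 to 5 years: 0.12 / (−ln 0.88) = 0.12 / 0.1278 = 0.939
- A patient leaving at time u has an uncounted event by time t with probability S(u) − S(t), averaged over u
- Lost by year 5: 182 × (0.939 − 0.880) = about 11
- Lost by year 10: 182 × (0.939 − 0.774) = about 30
- Expected in the cohort: 1822 × 0.12 = 219 by year 5; 1822 × (1 − 0.774) = about 411 by year 10
- Shares: about 5% and 7%

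Multiplying person-years by hazard gives 182 × 2.5 × 0.0256 = 11.6 and 182 × 7.5 × 0.0256 = 35. This is too high, because it ignores that patients who have had an event are no longer at risk.

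If only a fraction w of drop-outs are withdrawers who allow collection, the loss is about 11w and 30w. With w = 0.5 it is about 5 and 15.

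**Outer bound on power.** Suppose drop-outs contribute no events at all and the 3% who die contribute none. At N = 1822 there are 1822 × 0.97 × 0.90 × 0.12 = 191 events and power is 71%. Recovering every drop-out event gives 1822 × 0.97 × 0.12 = 212 events and power of 76%. The true gain is smaller, since withdrawers do contribute events until they leave.

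**Bias, illustration only.** On the same extreme footing, let the drop-outs' risk be r times the 12% seen in those retained. The cohort risk is 0.9 × 0.12 + 0.1 × 0.12 × r: 11.4% for r = 0.5, 12.0% for r = 1, 13.2% for r = 2 and 14.4% for r = 3. The error can go either way, and the protocol gives no value for r.

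**The case against.** It can be said that the cut in 8.3 describes only the data gathered under the first request, with later outcomes handled elsewhere. The text does not support this. Section 8.3 is the only statement of who contributes what, and it makes no exception for patients who granted the second request.

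It can also be said that the loss was planned for, since the sample size is inflated for 10% drop-out. That is true of precision at 2255. It does not justify collecting outcomes and then excluding them, and it does nothing for bias. The gap between 2255 and the 1822 in the Study Summary is a separate matter.

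Two stronger readings are tempting, and the objections to them stand.

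- A reader might infer that non-attenders' events are also discarded. No passage says so. Only withdrawal of consent makes a patient withdrawn (section 4.3), section 8.3 cuts data only at withdrawal or death, and survival tracking is not tied to attendance. The two-letter rule also follows a telephone step and, read in sequence, concerns patients contacted by letter. How these patients are censored is a detail that a statistical analysis plan can settle.
- A reader might infer that censoring is informative and that risk is understated. Sicker patients may well be more likely to leave, but the protocol does not say so. Cox regression needs censoring to be independent only given the covariates in the model. If leaving is unrelated to risk, the cost is precision alone.

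It is also fair that the 10% is an undivided drop-out rate. The share who formally withdraw and then allow collection is unknown, so the event counts are ceilings.

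**Conclusion.** The contradiction between sections 8.3 and 4.3.2 for consenting withdrawers is certain from the text, and 8.3 as written discards primary-outcome events that patients agreed to have used. The stop at death is not part of this defect.

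The effect is modest. Under the upper-bound assumptions in the working, at most about 11 events go by year 5 and about 30 by year 10, and fewer in proportion if only some drop-outs are consenting withdrawers. Those ceilings also assume average risk in the leavers; the loss would be larger if their risk were higher. Bias in absolute risk and in the risk score is possible, but its direction and size cannot be derived from the protocol.

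For non-attenders there is only a point to clarify. This should be corrected because the loss is avoidable, not because it threatens the study.

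**What to change.** Amend section 8.3 along these lines: patients who withdraw but allow outcome collection contribute time-to-event outcomes up to the last date of consented outcome ascertainment; data of patients who decline are handled as section 4.3.2 already states (deleted). Keep the analysis cut at the withdrawal date as a sensitivity analysis.

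As a clarification only, state in section 4.3.2 that non-responders are lost to clinic assessment and stay under records and MRIS follow-up where their consent covers it. Section 4.2 describes consent to passing identifiable information to MRIS. Whether consent extends to GP and hospital records of non-responders should be checked against the consent form, which was not available for this review.

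The change to 8.3 costs one sentence and one extra analysis, and uses outcomes that 4.3.2 already plans to collect. The clarification costs one more sentence plus the consent check.
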